#### Secondary outcome measures

##### Cognitive functions

Subtests of the Wechsler Adult Intelligence Scale (WAIS) and the Wechsler Memory Scale (WMS) will be used to measure memory and cognitive functions. The subtests of WAIS will include digit symbol-coding (total score = 133) and matrix reasoning (total scale = 26). The WMS subtests will consist of facial recognition (total scale = 48), verbal paired associates (total scale = 32), word lists (total scale = 48), and spatial span (total scale = 32). The WAIS and the WMS have high reliability and validity and are often used to differentiate individuals with memory or cognitive deficits from those who are cognitively intact. The WAIS and the WMS can also be used to assess cognitive improvements after a specific intervention [40].

Useful Field of View (UFoV) is the visual area over which useful information can be obtained at a quick glance without eye or head movements. This UFoV will be assessed with the *Double Decision* game in the BrainHQ program. The participants will be asked to select a particular symbol shape located at the center while remembering the position of another image presented on the screen. The UFoV requires the abilities of visuomotor processing, divided attention, and selective attention [41].

Dual-task tests will be used to assess an individual’s ability to perform two tasks simultaneously. The dual-task test could reflect the attentional limitation, central executive ability, and automatic processing ability of the participant [42, 43]. The dual-task performance will be evaluated while the individual performs the 10-m Walk Test and the Box and Block Test (BBT). For the 10-m Walk Test, the participants will be asked to walk 10 m at their comfortable walking speed. The walking time and number of steps will be recorded. The BBT will be assessed with a wooden box containing two equally sized compartments. Cubes will be placed in one compartment, and the participants will be instructed to use their dominant hand to move the cubes to the other compartment one-by-one at their fastest speed. The number of cubes moved within 60 s will be recorded. The secondary cognitive task that will be performed during the 10-m Walk Test or BBT will be the counting task and the response time task. For the math calculation, the participants will be required to count backward by 7 from a given number (e.g., 100 or 200); for the response time task, the participants will be required to listen to a series of sounds and respond to a high- or low-pitch tone as fast as possible. The results of the dual-task tests will provide information about whether the two tasks compete for the same class of neural resources or one of the tasks can be carried out automatically [44].

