#### COG group

BrainHQ (Posit Science Inc., San Francisco, CA, USA) will be used to train different cognitive functions of the participants in the COG group. BrainHQ is a game-based computer program specifically designed to train various cognitive functions. This cerebral neuroplasticity-based computerized cognitive training program has been demonstrated to have significant benefits on various cognitive functions in community-dwelling older adults [33, 34]. During the training sessions, laptops with touchscreens will be provided to the participants so that they can play the computer-based games without having to manipulate a mouse. The BrainHQ games that involve cognitive functions of visuospatial processing, attention, memory, language, and logical thinking will be chosen for the participants to practice.

The participants will practice two to three games in 90 min, and the difficulty of the tasks will be adjusted to each individual's ability. The participants will not compete against each other but will play the games based on their own capability. The task will become more challenging as a participant improves. The intervention will contain 10 min of warm-up (explaining the rules), 70 min of cognitive training, and 10 min of cool-down (asking participants to recall and provide feedback to the activities). Each participant’s performance will be recorded in the daily log.

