#### SEQ group

The participants in the SEQ group will first perform 45 min of physical exercise, followed by 45 min of cognitive training. During the physical exercise session, the participants will engage in 5 min of warm-up, 35 min of physical exercise, and 5 min of cool-down. The physical exercise programs will involve 15 to 17 min of aerobic exercise and 18 to 20 min of balance training and muscle strengthening. During the cognitive training session, the intervention therapists will spend 5 min explaining the rules of the tasks. Then, the participants will engage in 35 min of cognitive training with the BrainHQ games, as described in the COG group. The participants will be given one or two games to practice during the training session. The session will end with 5 min of cool-down activities such as proving feedback and asking the participants to recall the activities.

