#### DUAL group

Participants in the DUAL group will be instructed to perform physical exercise and cognitive tasks simultaneously. Because dual-task training is a more challenging approach for participants with MCI, we have used PowerPoint presentations to design simpler versions of the BrainHQ games to make sure that the participants will be able to follow the instructions and engage in the games (Fig. 2). Similar to the COG and SEQ groups, the difficulty of the cognitive tasks will be adjusted as the participants improve in their performance. The physical exercises involved in this group will be carefully chosen to ensure that our participants can effectively perform the exercises while focusing on the cognitive tasks. The exercise programs will also include the components of aerobic exercise (e.g., stepping in place), balance training (e.g., static standing or walking), and muscle strengthening (e.g., using Thera-Band or weights). Examples of the dual-task training programs include practicing math calculations while stepping and search for a different bird on the screen (Fig. 2a) while strengthening the hip muscles with a Thera-Band.

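### UFoV is scored with a game from BrainHQ, the software COG and SEQ train on but DUAL and PE do not, so arm differences on this secondary outcome cannot be separated from practice

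*Protocol article*

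**What the plan says.** Under Secondary outcome measures, Cognitive functions, the protocol article fixes the instrument: "This UFoV will be assessed with the *Double Decision* game in the BrainHQ program". The same paragraph says what the test draws on: "The UFoV requires the abilities of visuomotor processing, divided attention, and selective attention".

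The Interventions section gives each arm its training:

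- **COG:** "BrainHQ (Posit Science Inc., San Francisco, CA, USA) will be used to train different cognitive functions of the participants in the COG group". Games are picked by domain: "The BrainHQ games that involve cognitive functions of visuospatial processing, attention, memory, language, and logical thinking will be chosen for the participants to practice". Each session holds "70 min of cognitive training".
- **SEQ:** after the exercise half, "the participants will engage in 35 min of cognitive training with the BrainHQ games, as described in the COG group".
- **DUAL:** "we have used PowerPoint presentations to design simpler versions of the BrainHQ games". Each session has two exercise-plus-cognition blocks with 35 min of training apiece. The two games illustrated in Fig. 2 are a visual search task that asks for a location and a divided-attention task.
- **PE:** aerobic, balance and strength work, with no cognitive software.

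The article does not say whether Double Decision is among the games practised.

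**The concern.** An outcome taken from the training software in two arms, and from unfamiliar software in the other two, does not measure the arms on equal terms. The Background itself reports from a systematic review that the gains from cognitive training fall mainly on the tasks that were practised. UFoV enters the trial as a measure of executive function (Sample size estimation), so a difference between arms invites the reading that attention or executive function improved.

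Two aims are touched. Aim 3 compares sequential with simultaneous training, and SEQ uses BrainHQ while DUAL does not. Aim 2 compares combined with single-mode training. There the bias can run either way: SEQ v PE could be flattered by practice, while SEQ v COG and DUAL v COG could be pulled down by COG's larger exposure.

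**Working it through.** The plan states no figure on this point, so there is none to reproduce. The check has three steps.

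**1. Would the selection rule admit the test game?** COG games are chosen from domains that include visuospatial processing and attention. The UFoV paragraph says the test needs visuomotor processing and divided and selective attention. The domains overlap, so the rule as written would admit Double Decision, and the article does not reserve it for testing. Admissible is not the same as used: practice on the game itself is possible, whereas familiarity with the software is certain in COG and SEQ.

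**2. Scheduled exposure.** Training minutes per session (Interventions) × 36 sessions (Study design and procedures):

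| Arm | BrainHQ software | Simplified PowerPoint copies |
|---|---|---|
| COG | 70 × 36 = 2520 min = 42 h | 0 |
| SEQ | 35 × 36 = 1260 min = 21 h | 0 |
| DUAL | 0 | up to 2 × 35 × 36 = 2520 min = 42 h, during exercise |
| PE | 0 | 0 |

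Exposure to the test platform thus differs in SEQ v DUAL (21 h v 0), SEQ v PE (21 h v 0), SEQ v COG (21 h v 42 h) and DUAL v COG (0 v 42 h).

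**3. How often would practice alone give a significant result?** Inputs: n = 16 per arm (the figure in Sample size estimation before the dropout allowance), two-sided α = 0.05 (Data analysis), and an assumed net practice lift d, in SD units, of SEQ over the comparator with no transfer. The lift is an assumption; the article gives no practice effect.

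For a two-sample t test, df = 2 × 16 − 2 = 30, the critical value is 2.042, and the noncentrality is d × √(16/2) = 2.828d. The probability of significance is P(|T| > 2.042) under the noncentral t distribution.

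| Assumed lift d | Noncentrality | P(significant) |
|---|---|---|
| 0.2 | 0.57 | 8.5% (about 9%) |
| 0.21 | 0.59 | 8.9% |
| 0.5 | 1.41 | 27.8% |
| 0.8 | 2.26 | 59.1% |

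The row for 0.21 is there because that is the only UFoV effect size in the article, taken from the study of sequential exercise and mental activity; it is a treatment effect, not a practice effect. The same arithmetic applies to SEQ v PE. It is a comparison of two arms at one time point and does not model the planned repeated-measures ANOVA, so it shows scale only.

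**The case against.** **The game may never be trained.** An article commonly leaves the list of games to the intervention manual, so its silence does not show that Double Decision is practised. A reader might infer that participants are trained on the test itself; the article does not support that. Nor does it support a shared device or mode of response: it says that "laptops with touchscreens will be provided to the participants so that they can play the computer-based games" in training but does not describe the device used for the UFoV test. What stands is that the outcome is part of the training software in two arms, and that the stated rule would admit the game.

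**DUAL is not naive.** DUAL may spend up to 42 h on simplified copies of BrainHQ games, and the illustrated ones draw on abilities close to those UFoV needs. This stands. It narrows the gap between SEQ and DUAL and lowers the percentages above. It does not give DUAL the software, and PE has neither.

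**A practice gain is a real score difference.** It is tempting to call this an inflated type I error. It is not: the test would correctly detect a difference in scores. The problem is what that difference can be said to mean.

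**Assessors are blinded.** True, but blinding of evaluators does not remove the participants' own practice.

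**Only one secondary outcome is affected.** This stands and limits the weight of the point. The MoCA, the Stroop test and the WAIS and WMS subtests are not BrainHQ games. A reader might extend the concern to the primary conclusions; nothing in the article supports that. COG v PE, being single mode against single mode, is also not a contrast that aim 2 asks about.

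**Conclusion.** The concern holds for UFoV alone. As written, the plan gives COG and SEQ 42 h and 21 h on the software that carries the test and gives DUAL and PE none. A SEQ advantage over DUAL or PE on UFoV therefore cannot be separated from practice, and COG's larger exposure could mask a benefit of combined training.

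The size cannot be fixed from the article. Under an assumed net lift of 0.2 to 0.8 SD with 16 per arm, practice alone would make SEQ v DUAL significant in about 9% to 59% of trials. The low end is barely above the nominal 5%, and DUAL's related practice moves the answer towards it. The conclusion does not depend on Double Decision having been practised; if it has been, the case is stronger. The point is worth correcting because the correction is cheap, but it does not threaten the primary analysis.

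**What to change.** 1. In the COG and SEQ intervention sections, state that Double Decision is reserved for testing and is not used for training in any arm. Submit this as a modification to the review board and the registry, as Data management and monitoring requires. Trial status reports 39 of 80 recruited, so 80 − 39 = 41 were still to come.
2. In the UFoV paragraph, state that UFoV is a trained-platform outcome for COG and SEQ and will not be taken as evidence of transfer for aims 2 and 3. Leave that claim to the Stroop test and the WAIS and WMS subtests. This statement is needed even with step 1, because withholding one game does not remove familiarity with the software.
3. Keep the UFoV analysis of all randomised participants as the main one. If the therapists' daily logs name the games played, which the article does not say, report how many participants practised Double Decision in each arm. Any analysis without them must be labelled exploratory: it would remove people from COG and SEQ only, after randomisation, and so break the randomised comparison.

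The cost is one fewer training game, a modification submitted mid-trial so that the game menu may differ between earlier and later participants, and a more modest claim for one secondary outcome.

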##### Physical functions

The Timed Up and Go (TUG) test will be used to assess mobility and dynamic balance ability. The participants will be required to stand up from a chair, walk 3 m at their comfortable speed, turn around, then walk back to the chair and sit down. The time to complete the TUG test has been shown to be a good indicator to detect potential people who are likely to fall and frail older people [45]. The test-retest reliability of the TUG on individuals with cognitive impairment is excellent [46].

The 30-s Chair-Stand Test (CST) will be assessed to indicate the strength and endurance of the lower extremities. The participants are asked to stand up from a standardized chair and then sit down as many times as possible within 30 s. The feasibility and reliability of using the CST in people with cognitive impairment have been established to be good [46].

The Chinese version of the International Physical Activity Questionnaires (IPAQ) is an international measure for health-related physical activity. This study will use a short form of the IPAQ to assess changes in physical activity before and after the intervention. The reliability and validity of the IPAQ has been established across 12 countries [47].

ActiGraph GX3 accelerometers (ActiGraph, Shalimar, FL, USA) will be used to measure physical activity outside the laboratory settings [48, 49]. The participants will be asked to wear the actigraphy on both wrists all day for three consecutive weekdays before and after the intervention. The number and average counts of movement per minute for the participants will be recorded and calculated by the accelerometer. Data recorded by the actigraphy will be analyzed using MAHUFFE software (http://www.mrc-epid.cam.ac.uk/). The use of actigraphy to measure arm use and physical activity has been established for older people [50].

Decreased muscle mass, muscle strength, and movement quality are related to the aging process that will affect physical activities in older adults [51]. Therefore, muscle strength will also be recorded on both sides for knee extension, knee flexion, and grip strength using a handheld dynamometer (Commander Power Track Muscle Dynamometer Manual Muscle Tester, JTECH Medical) and a Jamar Handgrip Dynamometer.

##### ADLs, quality of life, and social participation

The ADLs will be assessed with the Chinese version of the Disability Assessment for Dementia (DAD), a questionnaire for evaluating the basic ADLs and instrumental ADLs in participants in the early stages of dementia. The DAD subtests include hygiene, dressing, continence, eating, meal preparation, telephoning, going on an outing, finance and correspondence, medications, and leisure and housework. The DAD assesses an individual’s performance from the perspectives of initiation, planning and organization, and effective performance [31].

In addition, the Chinese versions of the Barthel Index (BI) and the Lawton Instrumental Activities of Daily Living Scale (Lawton IADL) will be assessed. These questionnaires measure the performance of feeding, grooming, bathing, toileting, transferring, and tool using, among others. The BI and the Lawton IADL are both commonly used to evaluate older adults with cognitive impairment [52].

The treatment effects on quality of life will be assessed with the Chinese versions of the Quality of Life in Alzheimer’s Disease Instrument (QoLAD), the Caregiver Burden Inventory (CBI), and the short form of the Geriatric Depression Scale (GDS). The Chinese versions of these assessments have good reliability and validity [53–55].

Finally, social participation will be assessed with the Community Integration Questionnaire (CIQ), which measures items relevant to home integration, social integration, and productive activities [56]. The reliability and validity of the CIQ have been established in patients with traumatic brain injuries and stroke [56, 57].

### Data analysis

We will use analysis of variance (ANOVA) and χ^2^ to analyze differences in baseline characteristics and baseline outcome measures among the groups. Any differences among the groups in the baseline sociodemographic variables will become covariates in the subsequent statistical analysis. Repeated measures ANOVA will be used to determine the intervention effects for the four groups. A significant statistical level will be set at 0.05 for all comparisons. Besides *p* values, effect size η^2^ will also be calculated to determine the group difference for each outcome measure. An η^2^ greater than 0.138 is considered to be a large effect, an η^2^ between 0.138 and 0.059 is a moderate effect, and an η^2^ between 0.01 and 0.059 is a small effect [58]. Intention-to-treat will be used for missing data. Data analysis will be performed with PASW Statistics 18.0 software (IBM Corp., Armonk, NY, USA).

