### Study design and procedures

This proposed study is a randomized controlled trial with pretest, posttest, and 6-month follow-up assessments (Fig. 1). The study protocol is approved by the Chang Gung University Institutional Review Board. Intervention therapists will screen for potential participants and obtain signed informed consents from the eligible individuals before they participate in the study. The enrolled participants will be randomly assigned into the COG, PE, SEQ, or DUAL group with the allocation ratio of 1:1:1:1 [31]. Random tables based on the type of recruitment site (day care centers versus nursing homes versus community) will be generated by an independent research assistant using the web-based Research Randomizer tool (freely available at http://www.randomizer.org/) [32]. The research assistant will use the random table to decide the group allocation of a newly enrolled participant and will inform the relevant therapist to carry out the respective intervention. The intervention therapist will not know the group allocation until the pretest measurement is completed. Each intervention group will consist of three to five participants and will be guided by a trained therapist. The participants will engage in 90 min of training, two to three times a week, for a total of 36 training sessions.

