### Outcome measures

Sociodemographic variables, including age, gender, education level, comorbidity, smoking, alcohol intake, and depressive symptoms, will be recorded during the initial evaluation. This study will assess the participants before, immediately after, and 6 months after the intervention programs. The outcome measures will include several domains: cognitive functions, physical functions, ADLs, quality of life, and social participation.

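### Covariates are chosen by testing baseline sociodemographic differences, and baseline cognition is never one of them, so the model is not fixed in advance and gives up precision

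*Protocol article*

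**What the plan says.** The Data analysis section applies ANOVA and chi-square tests "to analyze differences in baseline characteristics and baseline outcome measures among the groups". It then gives the covariate rule: "Any differences among the groups in the baseline sociodemographic variables will become covariates in the subsequent statistical analysis". The rule has no threshold of its own, but the section later says: "A significant statistical level will be set at 0.05 for all comparisons".

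The candidates are listed under Outcome measures: "Sociodemographic variables, including age, gender, education level, comorbidity, smoking, alcohol intake, and depressive symptoms, will be recorded during the initial evaluation". That is seven named variables. MoCA, Stroop and recruitment-site type are not among them.

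For the treatment effect, the Data analysis section says: "Repeated measures ANOVA will be used to determine the intervention effects for the four groups". Study design and procedures describes a "randomized controlled trial with pretest, posttest, and 6-month follow-up assessments", so the pretest is one of three time points. The same section says of allocation: "Random tables based on the type of recruitment site (day care centers versus nursing homes versus community) will be generated".

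**The concern.** Between randomised groups, a significant baseline difference shows only that chance produced it. It does not show that the variable predicts the outcome, which is the reason to adjust for a variable. A selector of this kind can admit an irrelevant covariate and pass over a prognostic one whose imbalance falls short of significance in small arms. It also leaves the model for both primary outcomes unknown until the data have been seen.

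The rule is lopsided as well. Baseline outcome measures are tested, but nothing follows from the result, because only sociodemographic differences lead to adjustment. A participant's own baseline score is usually the best available predictor of the later score, and the trial already collects it. What is at stake is pre-specification and precision in a trial planned on 16 evaluable participants per arm.

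**Working it through.** **Sample size per arm.** Sample size estimation averages 5, 12 and 32 per group: 49/3 = 16.3, taken as 16. With 20% dropout, 16/0.80 = 20 per group, and 4 × 20 = 80. The stated figures reproduce, and 16 per arm is used below.

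**Chance that the rule admits a covariate.** Inputs: seven variables (Outcome measures) and the 0.05 level (Data analysis). Assumption: the variables are independent.

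1 − 0.95^7 = 1 − 0.698 = 0.302.

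A simulation with four arms of 16 and 2,000 runs gave 0.32 for at least one covariate and 0.05 for two or more.

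**Imbalance that the rule misses.** For a normal baseline variable in four arms of 16, simulation found the two most extreme arms more than 0.5 SD apart with a non-significant ANOVA in about 44% of trials. The planning effects in Sample size estimation are d = 0.21, 0.45 and 0.63, so such gaps are of similar size to the effects sought.

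**Type I error under the rule.** In a simulation of the rule itself (four arms of 16, seven independent candidates selected at p < 0.05, group test on pre/post change, 6,000 runs), type I error was 0.052, 0.050 and 0.046 for candidates with no, weak and moderate prognostic strength (0, 0.1 and 0.25 SD each). There was no inflation.

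**Efficiency.** Take unit variance at each visit and pre/post correlation r. With two visits the group-by-time test is a test on change.

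- Variance of change: 2(1 − r)
- Residual variance after baseline adjustment: 1 − r²
- Ratio: (1 − r²)/(2(1 − r)) = (1 + r)/2
- Per-arm size that 16 adjusted participants are worth in a change analysis: 16/ratio

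The documents give no r, so a range is shown. Two-arm power uses d = 0.45, taken in SD units of the raw score, with 16 per arm.

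| Assumed r | Change | Adjusted | Ratio | 16 per arm is worth | Power, change | Power, adjusted |
|---|---|---|---|---|---|---|
| 0.3 | 1.40 | 0.91 | 0.65 | 24.6 | 0.19 | 0.27 |
| 0.5 | 1.00 | 0.75 | 0.75 | 21.3 | 0.25 | 0.31 |
| 0.7 | 0.60 | 0.51 | 0.85 | 18.8 | 0.38 | 0.43 |
| 0.8 | 0.40 | 0.36 | 0.90 | 17.8 | 0.52 | 0.56 |

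At r = 0.5 and 0.7 the gain equals 1/0.75 = 1.33 and 1/0.85 = 1.18 times the participants.

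**Four arms and three visits.** Simulated power with both combined arms shifted by d = 0.45 (2,000 runs per setting):

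| Assumed r | Three-visit group-by-time | Posttest change | Posttest adjusted for baseline |
|---|---|---|---|
| 0.3 | 0.19 | 0.20 | 0.30 |
| 0.5 | 0.28 | 0.29 | 0.36 |
| 0.7 | 0.46 | 0.45 | 0.51 |
| 0.8 | 0.64 | 0.62 | 0.67 |

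With no true effect, all three tests stayed near 0.05 (0.045 to 0.053).

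**Recruitment-site type.** A balanced stratum explaining an assumed 20% of score variance left the unadjusted change test at a type I error of 0.050. A test on posttest values alone, without the stratum, fell to 0.021, which is conservative. Stable site differences therefore cancel in the planned group-by-time test. They matter once posttest values become the response.

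**The case against.** The strongest reply is that nothing here makes the planned test invalid, and that is correct. Three stronger readings are tempting, and the documents do not support them.

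- **Inflated false positives.** A reader might take the 30% as an error rate. It is the chance that a covariate enters the model, not the chance of a false treatment claim. Simulated type I error under the rule stayed near 0.05.
- **Uncorrected baseline imbalance.** A reader might infer that baseline cognition is ignored. It is not: the pretest is a time level, so the group-by-time test in effect subtracts it. Subtraction is less efficient than regression on baseline and over-corrects for regression to the mean, but it is a correction.
- **Site differences in the error term.** Stable differences in level between, say, community and nursing-home participants cancel within subjects. Only site differences in change over time could remain, and the protocol gives no sign of these. In addition, the article is condensed: that it names no site term does not show that the full plan lacks one.

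It is also fair to say that the gain depends on an assumed correlation and is modest when that is high: 10% of variance at r = 0.8. Which sociodemographic covariates to fix is a judgement that the documents do not settle.

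The covariate rule itself survives these replies. It is stated outright, and a plan that followed it would inherit the problem.

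**Conclusion.** The point holds as one of pre-specification and efficiency, and it should be fixed. It is not a validity defect. The covariate set depends on chance baseline differences: about a 30% chance that at least one of seven enters, assuming independence and the 0.05 level. The list is introduced as non-exhaustive, so more candidates would raise that figure.

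Baseline MoCA and Stroop cannot become covariates under the rule. Against a change-type analysis this forgoes 10% to 35% of the variance for r from 0.8 to 0.3, and 15% to 25% for r from 0.7 to 0.5. These figures assume equal variances at the visits and a correlation that the documents do not report. In four-arm power at d = 0.45 the difference from the planned three-visit test is about 0.46 against 0.51 at r = 0.7, and 0.28 against 0.36 at r = 0.5.

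**What to change.** In Data analysis, remove baseline significance testing as the means of choosing covariates and present baseline tables descriptively. For each outcome, pre-specify a model with the posttest and follow-up values as responses and that outcome's baseline value as a covariate, not as a level of the time factor. Include recruitment-site type as a fixed factor, because the random tables are based on it. Name any prognostic sociodemographic covariates now, chosen on subject-matter grounds and the same whatever the observed balance.

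All the variables are already collected, so the statistical cost is a few degrees of freedom. This does replace the analysis that the article names, so it needs a documented amendment before the final analysis. Trial status reports 39 of 80 participants recruited and 12 with completed follow-up, so there is still time.
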